## Abstract

**Background:**

A significant proportion of individuals are left with poor residual functioning of the affected arm after a stroke. This has a great impact on the quality of life and the ability for stroke survivors to live independently. While strengthening exercises have been recommended to improve arm function, their benefits are generally far from optimal due to the lack of appropriate dosing in terms of intensity. One way to address this problem is to develop better tools that could predict an individual’s potential for recovery and then adjust the intensity of exercise accordingly. In this study, we aim at determining whether an individualized strengthening program based on the integrity of the corticospinal tract, as reflected in the amplitude of motor evoked potentials (MEPs) elicited by transcranial magnetic stimulation (TMS), in conjunction with transcranial direct current stimulation (tDCS), could lead to more optimal outcomes in terms of arm function in chronic stroke patients.

**Methods:**

This multicentre, double-blinded, randomised controlled trial will aim to recruit 84 chronic stroke patients. Before and after training, participants will undergo a clinical evaluation, assessing motor recovery of the affected arm (Fugl-Meyer Stroke Assessment-FMA) and a TMS evaluation to assess the integrity of the corticospinal tract, as reflected in MEP amplitude. Based on their baseline MEPs amplitude, participants will be stratified into three groups of training intensity levels determined by the one-repetition maximum (1RM); 1) low: 35–50% 1 RM (MEPs < 50 μV); 2) moderate: 50–65% 1RM (MEPs 50-120 μV); and 3) high: 70–80% 1RM (MEPs > 120 μV). Training will target the affected arm (3 times/week for 4 weeks). In addition, participants will be randomly allocated into two tDCS groups (real vs. sham) and tDCS will be applied in an anodal montage during the exercise.

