### Sample size and power calculations

A priori power analysis was performed in G*Power 3.1.9.2, using a two-tailed independent samples t-test having an alpha level of 0.05, to calculate the sample size required in this study. By stratifying participants based on their MEP amplitude to provide an appropriate dosage of training, we expect all participants within the three MEP strata to benefit from the 4-week tailored strength training program. The sample size was thus calculated based on the expected difference in motor function gains between the tDCS real and the tDCS sham groups. Based on the results of studies having used repetitive application of tDCS in chronic stroke survivors, we expect an 8-point gain in FMA for the tDCS real group [56]. Furthermore, preliminary results based on this study showed a 7-point gain on the FMA scale after 4 weeks of strength training for participants presenting pre-training MEPs. Therefore, we estimate that the tDCS sham group (including participants with and without MEP) will show at least a 6-point gain on the FMA scale, exceeding the 5-point gain minimal detectable change (MDC) of this scale [57]. Thus, with an estimated average difference in FMA gain between both groups of 2 points (SD = 3), with an effect size of 0.66 and a power of 85%, we calculated that a total of 84 participants will be needed to detect differences between groups. However, presuming an attrition rate of 20%, a total of 105 participants will be recruited for the purpose of this study.

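### The abstract gives 84 as the number to recruit, but the sample size section makes 84 the number needed for 85% power and 105 the number to recruit.

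*Protocol article*

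**What the plan says.** The Methods paragraph of the abstract describes the design and says the "randomised controlled trial will aim to recruit 84 chronic stroke patients". It mentions neither attrition nor a larger enrolment.

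The section on sample size and power calculations gives the full chain. The calculation was made "using a two-tailed independent samples t-test having an alpha level of 0.05", with a difference of 2 points in Fugl-Meyer (FMA) gain between real and sham tDCS and an SD of 3, and "with an effect size of 0.66 and a power of 85"%. From these inputs, "we calculated that a total of 84 participants will be needed to detect differences between groups". The section then adds that, "presuming an attrition rate of 20%, a total of 105 participants will be recruited for the purpose of this study".

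So 84 is a recruitment target in the abstract and a required number before attrition in the body. The body's recruitment target is 105.

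**The concern.** Both places describe recruitment to the same trial, and they differ by 105 - 84 = 21 participants, which is 20% of the larger figure. Only one can be the target. The section on study design and setting reports that recruitment is under way at three sites, so the number still matters in practice. It also matters for reporting: a trial that enrolled 84 would look complete against the abstract and 21 short against the sample size section.

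A statistical consequence could follow. The 84 comes from the power calculation with no allowance for loss. If it were used as an enrolment ceiling and the plan's own attrition occurred, the analysed number would fall below what 85% power requires.

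**Working it through.** **Inputs.** From the sample size section: two-sided two-sample t-test, alpha 0.05, difference 2, SD 3, effect size given as 0.66, power 85%, attrition 20%. From the section on randomisation and blinding: 1:1 allocation.

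**Effect size.** d = 2/3 = 0.667. The article's 0.66 is this value truncated, so both are carried below.

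**Method.** Exact power from the noncentral t distribution, with df = n1 + n2 - 2 and noncentrality d × √[n1·n2/(n1 + n2)].

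**Step 1: reproduce the 84.** With 42 per arm, df = 82 and √(42 × 42/84) = √21 = 4.583.
- d = 2/3: noncentrality 3.055, power 85.5%. This is the smallest equal-arm size that reaches 85%.
- d = 0.66: noncentrality 3.025, power 84.8%. Strictly, 43 per arm (86 in total) would be needed, a trivial rounding difference.

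The stated 84 therefore reproduces as the number that must be analysed.

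**Step 2: reproduce the 105.** 84/(1 - 0.20) = 84/0.8 = 105, and in reverse 105 × 0.8 = 84. The inflation is correct.

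**Step 3: read 84 as the number recruited.** 84 × 0.8 = 67.2, or about 67 analysed, split 34 and 33. Then df = 65 and √(34 × 33/67) = √16.75 = 4.092.
- d = 2/3: noncentrality 2.728, power 76.7%.
- d = 0.66: noncentrality 2.701, power 75.8%.

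**Side by side (two-sided t-test, alpha 0.05)**

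| Recruited | Analysed | Power, d = 2/3 | Power, d = 0.66 |
|---|---|---|---|
| 105 | 84 (20% lost) | 85.5% | 84.8% |
| 84 | 67 (20% lost) | 76.7% | 75.8% |
| 84 | 84 (none lost) | 85.5% | 84.8% |

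In the second row the chance of missing the planned effect is about 23-24%, against about 15% in the first. The last row is the other extreme, in which everyone recruited supplies post-training data.

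**The case against.** The strongest reply is that the design is not in doubt. The section that sets the sample size is explicit and correct, an abstract is only a summary, and a reader can resolve the conflict from the body alone. That stands, and it limits the point to a correction of the abstract. It does not remove the point, because the abstract does not merely shorten the body: it attaches a different number to the act of recruiting.

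Three stronger readings are tempting, and the article does not support them.

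- *The trial will be underpowered.* A reader might infer this from the abstract, but nothing says that the sites will stop at 84. The body plans 105. The loss is conditional.
- *The primary comparison is at risk.* The FMA is a primary outcome, but the last paragraph of the Background makes the effect of tailored strength training the primary goal and real versus sham tDCS the secondary aim. The power figures concern real versus sham tDCS because the trial was sized on it.
- *The sample size arithmetic is wrong.* Both 84 and 105 reproduce.

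Two limits on the figure of 76-77% also stand. First, the tDCS section keeps participants who are discontinued from the intervention in an intention-to-treat analysis. If some of them return for the post-training assessment, more than 67 contribute data, so 67 is the worst case under 20% attrition. It is still a fair reading, since inflating from 84 to 105 treats attrition as lost information. Second, the figure is for the t-test used in sizing, not for the 3 × 2 ANOVA in the statistical analysis section. It compares like with like against the stated 85%, but it is not the power of the planned analysis.

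**Conclusion.** The inconsistency is real and lies in the abstract. The body supports one reading only: recruit 105 to have 84 for analysis. The defect is modest, but it concerns a figure that the trial relies on.

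If recruitment did end at 84 and the full 20% were lost to analysis, power for real versus sham tDCS would be about 76-77%, some 8 to 9 points below the stated 85%. This rests on the article's own difference, SD, alpha, allocation and attrition, and on the two-sample t-test. With no loss of data from the 84, power would stay at about 85%, so the shortfall lies between nothing and 9 points according to how many of those who leave still give post-training data.

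**What to change.** Correct the abstract to say that 105 participants will be recruited to obtain 84 evaluable, and use that target wherever enrolment is stated, including what the sites are told. If 84 is in fact the most that will be recruited, correct the sample size section instead: remove 105 as the target and state that, with 20% lost, power for the real-versus-sham t-test comparison is about 76-77%.

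The first option is a change of wording. It costs nothing if the sites already work to 105, and it alters no analysis, eligibility, randomisation or outcome rule. If they have been working to 84, keeping the planned power under 20% attrition means recruiting 21 more participants.

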**Discussion:**

This study will determine whether an individualized strength training intervention in chronic stroke survivors can lead to improved arm function. In addition, we will also determine whether combining anodal tDCS over the lesioned hemisphere with strength training can lead to further improvement in arm function, when compared to sham tDCS.

**Trial registration:**

ClinicalTrials.gov Identifier: NCT02915185. Registered September 21 2016.

## Background

Stroke is a leading cause of severe long-term disability across the globe [1, 2]. One of the most common disabling consequences of stroke is residual muscle weakness or paresis of the affected arm [3, 4], which has a significant impact on patients’ activities of daily life and is a major contributor to reduced quality of life [5, 6]. Consequently, there has been a move to implement strength training as part of rehabilitation after stroke [7], to increase strength and improve function of the affected arm, even at the chronic stage where gains are still observed [8]. Strength training is commonly used with progressive resistance or repetitive practice and there is evidence demonstrating that it is an effective intervention to improve strength and activity after stroke [7, 9]. Yet, variability is observed between individuals, in which some patients demonstrate significant gains in response to strength training programs while others show either minimal or no benefits [3, 10]. This brings to question whether the intensity of strength training programs is sufficient to produce a training stimulus and challenge individuals’ maximum capacity. Although there is a variety of strengthening protocols prescribed to stroke patients, few studies in the rehabilitation literature assess critical training parameters to address each individual’s needs and impairments [11, 12]. A meta-analysis by Coupar et al. [13] found that neurophysiological factors, such as the integrity of the corticospinal tract assessed by non-invasive brain stimulation (NIBS) techniques, were strongly associated with upper limb recovery after a stroke; supporting the use of neurophysiological markers in determining a person’s potential for recovery and functional performance. Thus, there is an urgent need to identify valid biomarkers of recovery to design better training interventions for the management of post-stroke disability, notably by adapting programs to meet each individual’s capacity in terms of potential for recovery.

Transcranial magnetic stimulation (TMS) is a NIBS technique allowing the identification of biomarkers reflecting the integrity of the corticospinal system after a hemispheric stroke [14]. Stimulation of the motor cortex can elicit motor evoked potentials (MEPs) in contralateral limb muscles, whose presence after a stroke is strongly suggestive of preserved functional projections and potential for recovery in the affected limbs. For instance, Jo et al. [15] reported that the presence of MEPs from both hand motor cortices in the early subacute phase was a good predictor of motor function in patients at 3 months after stroke onset. The combining use of TMS and tractography on 53 patients with intracerebral hemorrhage and severe motor weakness showed that patients in whom MEPs could be elicited in the paretic upper limb, and with a preserved corticospinal tract, had better motor outcomes at 6 months post-stroke [16]. On the other hand, other studies have reported that absence of MEPs in response to high intensity TMS of the ipsilesional motor cortex was associated with poor motor recovery of the upper limb in both the acute and chronic stages post stroke [17–19]. In addition to their ability to predict motor recovery, MEPs can also provide information on an individual response to exercises [20]. Several studies have highlighted the importance of this measure not only to assess corticospinal tract integrity to predict patients’ potential for recovery but also to predict their response to exercise [18, 21, 22]. Stinear et al. [18] for example, proposed an algorithm that uses MEPs as a marker for stroke survivors’ stratification in terms of exercises prescription to optimise functional recovery. Among the various parameters included in the algorithm, such as DTI and the presence of movements at the thumb and shoulder joints, the absence/presence of MEPs in response to TMS from the ipsilesional motor cortex was considered as a crucial parameter to consider in order to stratify patients based on their recovery potential.

In parallel, recent developments in the management of stroke disability indicate that further gains in function can be obtained when rehabilitation interventions are combined with neurostimulation techniques designed to boost motor excitability and enhance response to exercises [23]. The modulation of cortical excitability by transcranial direct current stimulation (tDCS) has gained particular interest because of its promising effects in neurorehabilitation after stroke [24], which include change in cortical excitability [25–27], enhancement of motor performance and change of movement accuracy and speed [28, 29]. The technique aims at modulating neuronal excitability using a constant and weak current (1–2 mA) which passes through electrodes placed on the scalp. Depending on the current direction, the stimulation can either enhance (anodal) or depress (cathodal) the excitability of the stimulated cortical area [30]. A number of studies have investigated the impact of anodal tDCS on motor recovery of the affected upper limb of stroke patients [31]. Kim et al. [32] stimulated the ipsilesional cortical region of 10 subacute stroke patients on average 12 weeks post infarct and reported significant improvement in motor performance of the hemiparetic hand, outlasting the stimulation session for at least 60 min. Similar results were obtained by Fregni et al. [33] and Hummel et al. [34], where stroke patients were found to have functional improvement in the paretic hand that outlasted the stimulation period with an improvement magnitude of 6.7 and 8.9%, respectively. Furthermore, results from a meta-analysis [35] also support the therapeutic potential of tDCS as an adjuvant treatment strategy to enhance training in stroke patients with upper limb deficits, where tDCS demonstrated a significant impact on rehabilitative training with a moderate effect size of + 0.52 (*p* < 0.001) and + 0.69 (*p* < 0.001) for both immediate and longer-lasting analyses (up to 6 months), respectively.

According to the existing literature, there is a clear need to further validate the use of MEPs as a classification tool and to explore new ways on how to refine the use of this measure, in order to optimize post-stroke training interventions. In addition, since tDCS is still relatively new in the field of stroke rehabilitation, no study to date has tried to determine whether tDCS can enhance the effects of a strength training intervention in stroke patients; a type of intervention commonly used in rehabilitation [3]. Ultimately, there is an urgent need to design better training interventions for the management of post-stroke disability, notably by adapting programs to meet each individual’s capacity in terms of potential for recovery. There is also an important need to determine whether non-invasive brain stimulation techniques, such as tDCS, can be used in conjunction with tailored strength training exercises to boost functional recovery after stroke.

The primary goal of this RCT is to determine whether a 4-week tailored strength training program could lead to improved arm function in chronic stroke survivors. The secondary aim is to determine whether combining anodal tDCS of the lesioned hemisphere with strength training could lead to further improvement in arm function when compared to sham tDCS. This study will help determine whether tailored strength training interventions in stroke survivors, based on MEPs amplitude, can lead to greater gains in arm function. In addition, it will also establish whether combining anodal tDCS with tailored strength training can further promote recovery in stroke survivors when compared to sham tDCS.

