
### Intervention period

All subjects will participate in an outpatient supervised tailored strength training program, which will follow the recommendations of the American Stroke Association (ASA) position on exercise prescription after stroke [47]. Specifically, it will be a 4-week training intervention, performed 3 times per week non-consecutively, with 3 series per exercise of 10 repetitions and a 2-min break in between exercises. The strength training program will be conducted for 1 h in an outpatient rehabilitation setting and supervised by an experienced trainer who will closely monitor the participants’ exercise performance. The training will commence with a 5-min warm-up comprising of active movements of the muscles to be trained. Using free weights, the one-repetition maximum (1RM), which is the maximum amount of weight load an individual can lift for one repetition, will be estimated by the 10RM [48] in order to avoid tendino-muscular injuries and fatigue. The 10RM will be determined for the muscles playing a key role in the functional performance of the upper limb [49, 50]. These muscles are the wrist extensors and the elbow and shoulder flexors. In addition, the grip muscles of the affected hand will be trained with a JAMAR® dynamometer. Participants’ maximal grip force will be determined and used to dose the training of the hand muscles and its progression.

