### Statistical analysis

Descriptive statistics will be used to characterize the sample. We will verify if, at the beginning, the two tDCS groups will be comparable by using independent t-tests or Chi-squared tests, depending on the nature of the variables. To evaluate the impact of tailored exercises based on MEP stratification on changes in FMA and MEP measures, as well as the impact of tDCS on enhancement of training response, a two-way 3X2 ANOVA [MEP strata (three levels) and type of tDCS (2 levels)] will be used. The significance level will be set at 0.05. If an interaction is noted, paired *t*-tests will be used to locate any significant differences in each stratum with a Bonferroni correction for multiple tests (adjusted *p*-value of 0.02).

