## Discussion

This study will be the first RCT to integrate a commonly used rehabilitation treatment, which is a strength training program of the affected arm, with state-of-the-art brain evaluation protocols and neurostimulation techniques (TMS and tDCS) to allow optimization of the intensity of training based on each stroke survivor’s recovery potential. This study will create an initial, yet strong evidence base for MEP stratification as a tool to guide clinicians in providing optimal tailored exercise programs to support recovery post-stroke. More importantly, the marked expected improvement in the affected upper limb’s motor function, following the tailored strength training program, will allow stroke survivors to have a more active lifestyle and ultimately optimal quality of life.

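### The stated primary goal (does MEP-tailored training improve arm function?) has no randomised comparator, and the planned 3×2 ANOVA does not test it

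*Protocol article*

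**What the plan says.** **Aims (Background).** The first aim is the effect of training: "The primary goal of this RCT is to determine whether a 4-week tailored strength training program could lead to improved arm function". tDCS comes second: "The secondary aim is to determine whether combining anodal tDCS of the lesioned hemisphere with strength training could lead to further improvement in arm function". The same paragraph adds a comparative claim without naming the comparator: "This study will help determine whether tailored strength training interventions in stroke survivors, based on MEPs amplitude, can lead to greater gains in arm function".

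**Design.** Under Intervention period, "All subjects will participate in an outpatient supervised tailored strength training program". Under Randomisation and blinding, the 1:1 allocation is to real or sham tDCS within MEP strata; nothing else is randomised. Baseline MEP amplitude sets the training intensity, with one range for each of the three strata.

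**Sample size.** Benefit from training is taken as given: "we expect all participants within the three MEP strata to benefit from the 4-week tailored strength training program". The calculation then rests on the real-versus-sham difference in FMA gain.

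**Analysis.** The 3×2 ANOVA (three MEP strata by two types of tDCS) has two stated purposes. One is the impact of tDCS. The other is this: "To evaluate the impact of tailored exercises based on MEP stratification on changes in FMA and MEP measures". Paired t-tests within strata follow only when an interaction is found.

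**Discussion.** "This study will create an initial, yet strong evidence base for MEP stratification as a tool to guide clinicians".

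**The concern.** The question called primary is neither randomised nor powered, and no term in the stated analysis tests it. The question called secondary is all three.

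The risk lies in how the result is read. The Statistical analysis section presents the ANOVA as the evaluation of tailoring, and the term that looks relevant is the stratum main effect. That term compares gains between three groups formed by a baseline prognostic marker, each trained at its own intensity. The Background itself cites evidence that MEPs predict recovery and response to exercise, so a difference between strata is expected from prognosis alone. A significant stratum effect therefore says nothing about tailoring. A non-significant one does not separate training that works equally well everywhere from training that does nothing. Either result could end up supporting the Discussion's claim about MEP stratification as a clinical tool.

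**Working it through.** **1. The plan's own figure.** Inputs from Sample size and power calculations: difference 2 points, SD 3, effect size 0.66, two-sided alpha 0.05, power 85%, attrition 20%.

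- With d = 2/3, the noncentral t calculation needs 41.4, so 42 per group and 84 in total. Power at 42 per group is 85.5%.
- With d = 0.66, it needs 42.2 per group. Power at 42 per group is 84.8%.
- Attrition: 84 / (1 − 0.20) = 105.

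Both 84 and 105 reproduce. They belong to the tDCS contrast only.

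**2. Randomised information on training.** Participants allocated to no training or to untailored training: 0 of 84 (0 of 105).

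**3. What the ANOVA terms respond to.** Write the change score in stratum s and tDCS group t as y = μ + αₛ + βₜ + (αβ)ₛₜ + error. The F-tests concern α, β and αβ. Whether training is followed by improvement concerns μ, which none of them tests. Whether tailoring beats another regimen is not a parameter of the model, because no other regimen is observed in any stratum.

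Simulated rejection rates (14 per cell, equal strata assumed, SD 3, 20,000 runs per scenario, gains equal across strata):

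| Gain, sham / real | Stratum | tDCS | Interaction |
|---|---|---|---|
| 6 / 8 | 4.8% | 85.6% | 5.1% |
| 0 / 2 | 5.2% | 85.1% | 4.9% |
| 7 / 7 | 4.7% | 5.0% | 4.8% |
| 0 / 0 | 4.8% | 5.2% | 4.8% |

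Removing the whole 6-point training gain (first row to second) leaves the three rates unchanged apart from simulation error. The last column also shows how seldom the paired t-tests would be reached: about 5% of the time when the tDCS effect is the same in all strata.

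**4. Unequal gains.** Equal gains are a device for isolating μ; the plan does not predict them. It cites a 7-point gain in participants with MEPs and expects at least 6 points in a sham group with and without MEPs. If the sham mean is exactly 6 and strata are of equal size (an assumption), the stratum without MEPs gains 3 × 6 − 7 − 7 = 4 points. With 28 per stratum and SD 3, the noncentrality is λ = 28 × Σ(gain − mean)² / 9:

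- 4/7/7: Σ = 6, λ = 18.7, power about 97%.
- 5/7/7: Σ = 2.67, λ = 8.3, power about 72%.
- 6/7/7: Σ = 0.67, λ = 2.1, power about 23%.

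So the stratum test may well be significant. That would reflect MEP status and intensity together, and the design cannot separate them.

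**5. What a before-after estimate could show.** For the sham group at n = 42 with SD 3, the standard error is 3/√42 = 0.46. A 6-point mean gain is 6 / 0.46, about 13 standard errors from zero. Precision is not the obstacle; the lack of a control is.

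**The case against.** The strongest reply is that the primary goal, read literally, asks only whether training could be followed by improvement. That is a before-after question. The data are collected, the outcome is FMA change, and the 5-point MDC is cited as a benchmark. Participants are more than 6 months after stroke and have finished rehabilitation, which limits spontaneous recovery as an explanation. All of this stands. A reader might infer that the trial can answer nothing except the tDCS question; the documents do not support that. What they lack is a randomised answer about training, and a planned test of mean gain that does not wait for an interaction. Practice, attention and expectation would remain as explanations. The literal reading also does not rescue the promise of greater gains or the evidence base claimed for MEP stratification, since both are comparative.

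Two other inferences go too far. One is that the plan predicts equal gains and hence a null stratum effect. It predicts benefit in all strata without saying equal, and its figures point to unequal gains. The other is that evaluators know the time point. The article describes blinding to tDCS group and is silent on time point, which is not evidence either way.

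It may also be said that a separate analysis plan would settle this. It could add the missing estimate, but it cannot supply a comparator, and the article states outright that the ANOVA evaluates tailoring. Finally, the order of aims is partly the sponsor's choice. That is fair, provided the analysis matches the choice.

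**Conclusion.** The point holds. There is no randomised evidence on the stated primary goal, and the ANOVA offered as its evaluation has no term that addresses it. The only contrast both randomised and powered is real versus sham tDCS, labelled secondary.

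The structural part needs no assumptions: 0 participants are allocated to an alternative to tailored training, and there is one intensity range per stratum. The rejection rates and power figures assume equal strata, SD 3 for individual FMA change (as the plan's own calculation does) and normal errors. Other stratum sizes would move the power figures in step 4 but not the conclusion.

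The limits are equally clear. The sample size arithmetic is correct, the randomised tDCS estimate is not biased by any of this, and an uncontrolled estimate of the training gain is feasible and would be precise. The fault is a mismatch between the stated goal and the design, analysis and power, together with claims about tailoring that the design cannot support. It should be corrected before unblinding because, followed as written, the headline conclusion would rest on a test that cannot bear it.

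**What to change.** Before unblinding, by a dated amendment that gives its reasons:

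1. Make the real-versus-sham difference in FMA change the primary randomised comparison. At the least, state that it is the only confirmatory one.
2. Analyse the training aim unconditionally, labelled as an uncontrolled before-after estimate: mean FMA change with 95% CI overall, in the sham group, and in each stratum. The sham group shows training without active stimulation. Use the 5-point MDC as context, not as a test threshold.
3. State in Statistical analysis that the stratum F-test compares prognostic groups trained at different intensities and is not evidence for or against tailoring.
4. Reword the promise of greater gains in the Background and the claim about MEP stratification in the Discussion to what one intensity range per stratum can support.

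**Cost.** No extra patients and no new data. The price is a more modest claim about tailoring and a documented change in the order of objectives while recruitment, open since May 2017, is under way. A randomised answer about tailoring would need a comparator arm, which is a different trial and is not proposed here.
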